## Methods

This prospective, controlled, superiority trial compares outcomes of two parallel groups, namely an online intervention group and a waiting-list control group, randomly assigned in a 1:1 ratio, and a third, non-randomized ad hoc sample, namely a face-to-face intervention group.

Data for the online intervention group and the control group will be collected at the Institute for E-Counselling, University of Applied Sciences Nuremberg Georg-Simon-Ohm, Germany. The Institute is a department of the Faculty for Social Sciences. It is specialized in developing, implementing, and evaluating online counseling solutions. The partnering companies that will offer the online intervention to their employees include multiple plants of a large German engineering and technology company and two German municipal hospitals. Data for the face-to-face intervention group will be collected at the outpatient clinic for sleep medicine at the University Clinic for Psychiatry and Psychotherapy, Paracelsus Medical University Nuremberg, Germany, as well as partnering outpatient sleep clinics across Germany.

For the online conditions, participants are included starting in November 2019 and ending in May 2022, according to the eligibility criteria listed in Table 1. Prior to granting access to the online platform, company physicians or social counseling services will obtain informed consent. Participants will be anonymous to the CBT-I professional.

**Table 1 Tab1:** Eligibility criteria for participants

Inclusion criteria	
Age ≥ 18	
Regularly (> 6 times per month) working outside the hours of 6 a.m. to 10 p.m.	
Subjective sleep issues diagnosed in the screening process	
Exclusion criteria	
Acute suicidality as measured by the respective item in the BDI-II at T0	
Ongoing alcohol or drug abuse	
No access to required technology (PC, smartphone, tablet)^a^	

^a^Only applies to online conditions

For the face-to-face condition, collaborating clinics will include participants from August 2020 to May 2022. Most of the same eligibility criteria apply (see Table 1).

Both the online and the face-to-face intervention are based on CBT-I principles [32]. The online program consists of psychoeducation, sleep restriction, and stimulus control, all delivered via personalized e-mails, as well as relaxation techniques, delivered via text and audio files. The face-to-face intervention consists of the same contents, delivered in 45-min, one-on-one outpatient sessions. Psychoeducation includes presenting general information about sleep and sleep disorders in order to challenge misperceptions and faulty beliefs about insomnia and its consequences as well as sleep hygiene education. In sleep restriction, the CBT-I professional instructs participants to reduce their time in bed and adhere to regular bedtimes. This creates a mild state of sleep deprivation, ultimately increasing sleep quality and decreasing fragmentation of sleep. While following stimulus control, participants use their beds exclusively for sleep in an attempt to disassociate the bed with potentially stressful or exciting activities. This entails leaving the bed and the bedroom if wakefulness persists for more than 15 min and only returning to bed once sufficient sleepiness has set in. Relaxation techniques include breathing exercises and progressive muscle relaxation. Some parts of the program have been adjusted to better fit the needs of shift workers. Most importantly, we will not recommend strictly regular bedtimes, often referred to as sleep windows [32], and instead work with anchor sleep [38]. In this approach, participants are encouraged to find the longest possible overlap between the times they spend in bed during each 24-h cycle, irrespective of the specific shifts they work. For more detailed descriptions of the CBT-I contents, we refer to our feasibility study [29] and the primary literature [32].

After registration, T0 measurements and randomized allocation, participants in both of the online groups will receive access to the first weekly sleep diary along with instructions on how to proceed. Every time participants in the online intervention group complete a week of diary entries, they will receive the next e-mail with individual feedback and further CBT-I contents. In the face-to-face intervention, participants will fill out sleep diaries between sessions. We will encourage participants to leave as few nights undocumented as possible; however, breaks in the sleep protocols will be permitted. Following our experience from the feasibility study, we expect that participants complete the program within 6 to 12 weeks. We will consider an intervention complete after a participant has received all CBT-I contents and filled out at least 4 weeks of sleep diaries.

T0 will include screening questions for sleep issues such as periodic limb movement disorder, sleep apnea, and sleepwalking, as well as questions regarding concurrent and previous treatments. Changes in medication will be reported in the sleep diaries. We will not exclude participants from the trial based on these questions; however, we might recommend alternative courses of treatment and we will control for relevant changes in treatment or medication during the trial when analyzing the data.

Outcome measures of the study will include data from at least four sleep diaries (total sleep time and time in bed for each night, average sleep efficiency across seven consecutive nights) as well as psychometric self-report scales at T0 and T1. The BDI-II is a 21-item self-report measure for depressive symptoms [35]. The RIS is a 10-item self-report questionnaire for cognitive, emotional, and behavioral aspects of psychophysiological insomnia [36]. The ESS is an 8-item self-report scale for daytime sleepiness [37]. In addition, T0 will include the 15-item self-report Morningness-Eveningness-Stability-Scale improved (MESSi) [39], from which the individual chronotype will be calculated, as well as three screening questions for sleep apnea, snoring, and periodic limb movement disorder. This will be used to guide the CBT-I treatment and explore potential differences in treatment response [40].

Figure 1 and Table 2 illustrate the design of the study. For the online arms of the trial, company physicians and social counseling services in collaborating companies will screen those interested for eligibility. We describe inclusion and exclusion criteria in Table 1. Psychometric assessments are carried out on the online platform after logging on for the first time (T0) and after filling out the last of four weekly sleep diaries (T1). Immediately after T0, participants are allocated randomly in a 1:1 ratio to the intervention or the control group. The intervention group will receive the CBT-I contents via e-mail between their weekly sleep diaries (W1 through W4). After completing T1, participants in the waiting group will be able to follow the CBT-I program. If they choose to do so, they will complete at least four more sleep diaries during the CBT-I period and we will contact them for a follow-up (T2) after completion. For the face-to-face arm, psychologists and CBT-I professionals in collaborating outpatient sleep clinics will screen their patients for eligibility according to the criteria in Table 1. Psychometric assessments are carried out right before the first (T0) and right after the last session (T1) (see Table 2).

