**Methods:**

Collaborating companies will offer our anonymous online intervention to their shift-working employees. Company physicians and counseling services will screen those interested for inclusion and exclusion criteria. Participants will receive access to our online service, where they will complete psychometric assessment and receive random assignment to either the intervention group or the waiting-list control group. Participants and providers will be aware of the group assignment. We aim to allocate at least *N* = 60 participants to the trial. The intervention consists of psychoeducation, sleep restriction, stimulus control, relaxation techniques, and individual feedback delivered via four e-mail contacts. During the intervention, as well as during the waiting period, participants will fill out weekly sleep diaries. Immediately after completion of the program, the post-intervention assessment takes place. Participants in the control group will be able to participate in the program after all study assessments. To recruit an additional sample, collaborating outpatient sleep clinics will provide six sessions of standard face-to-face CBT-I to an ad hoc sample of shift working patients. We expect both the online and the face-to-face CBT-I interventions to have beneficial effects compared to the control group on the following primary outcomes: self-reported symptoms of depression and insomnia, sleep quality, and daytime sleepiness.

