The purpose of this study is to evaluate the effects of online CBT-I in shift workers, compared to a waiting-list control group and face-to-face CBT-I. Specifically, we hypothesize both CBT-I interventions to be associated with greater improvements than the control condition regarding the following outcomes: sleep efficiency as reported by the participants in sleep diaries [34]; symptoms of depression as measured by the Beck Depression Inventory (BDI-II) [35]; symptoms of insomnia as measured by the Regensburg Insomnia Scale (RIS) [36]; and daytime sleepiness as measured by the Epworth Sleepiness Scale (ESS) [37].

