Group assignment takes place immediately after receiving T0 measurements. The CBT-I professionals will assign their respective participants to the intervention and the waiting group in a 1:1 ratio using an Excel sheet, where every anonymous, randomly assigned access code has been randomly assigned a value of 0 or 1, corresponding to the waiting list and the intervention group respectively. Those responsible for data evaluation will be blinded regarding group assignments. Participants and providers will be aware of the assignment.

Participants will enter their baseline (T0) and outcome (T1) data described under Outcomes, as well as their sleep diaries through our online platform and transmit it to the Institute’s servers. We will contact participants that dropped out or otherwise failed to transmit four sleep diaries for T1 measurements.

Data will be exported from our servers and entered into SPSS [44] via the program’s syntax function. The raw data will remain on the servers for storage security. We will check the data for errors resulting in outliers or missing values. Missing values will not be replaced. Dropouts will be analyzed separately Group comparisons and superiority tests will be computed in SPSS using repeated measures ANOVA.

A data monitoring committee will not be needed, as the CBT-I professionals are not blinded during the trial and can react to any adverse events. The sleep restriction element of the CBT-I intervention is the only part of the trial where adverse events are expected to occur based on experiences from outpatient treatment with the same contents. If a participant reports issues in the form of a critical drop in total sleep time (< 4h for 7 nights or more) with this part of the treatment, CBT-I professionals are instructed to try to use a less strict approach. If this is still not tolerated well enough, we will stop sleep restriction and proceed with the rest of the contents. This should result in a quick recovery. Reports of adverse events will be collected alongside any other solicited or spontaneously reported feedback from participants. Interim analyses, trial conduct audits, and stopping guidelines are not intended at this point.

The study was approved by the ethics committee of the Lutheran University of Applied Sciences Nuremberg, Germany, under the trial ID am/sot. Changes to the protocol will be communicated to the sponsors, trials registry, and ethics committee within 6 months of their implementation.

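### Diary sleep efficiency has no pre-randomisation baseline in the online arms, and the timing of the four e-mails against the four diary weeks needs reconciling

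*Protocol article*

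**What the plan says.** The last paragraph of the protocol article's Introduction lists the hypothesised outcomes, beginning with "sleep efficiency as reported by the participants in sleep diaries". Methods, in the paragraph on outcome measures, takes this from at least four diaries as "average sleep efficiency across seven consecutive nights".

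The order of events is given twice in Methods. The paragraph on the study design says: "Immediately after T0, participants are allocated randomly in a 1:1 ratio to the intervention or the control group". The paragraph on the course of the program says: "After registration, T0 measurements and randomized allocation, participants in both of the online groups will receive access to the first weekly sleep diary". T0 as described holds scales and screening questions, not a diary. On blinding, the paragraph on group assignment says: "Participants and providers will be aware of the assignment".

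Three statements bear on the timing of the content:
- Abstract, Methods: "individual feedback delivered via four e-mail contacts".
- Methods, study design: "The intervention group will receive the CBT-I contents via e-mail between their weekly sleep diaries (W1 through W4". T1 is set after the last of four diaries.
- Methods, course of the program: "Every time participants in the online intervention group complete a week of diary entries, they will receive the next e-mail with individual feedback and further" material. Completion requires all content and a minimum of four diary weeks, with an expected duration of 6 to 12 weeks.

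The named analysis for group comparisons is repeated measures ANOVA, and the sample size calculation assumes two measurements.

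**The concern.** A repeated measures comparison asks whether the arms change differently from a common starting point. Randomisation guarantees that starting point only for values recorded before allocation. For sleep efficiency the earliest value is W1, reported by people who already know whether they are being treated or are waiting. If the first e-mail comes before or with W1, that week also contains some treatment.

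A contrast from W1 can then miss an early effect, or carry over a difference in reporting that arises from knowing the arm. Anyone who leaves between allocation and W1 has no sleep-efficiency value at all.

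The e-mail count raises a second question at the other end of the timeline. If the last content arrives after W4, no required diary week reflects the full program. T1 may then be taken too early as well, which would touch BDI-II, RIS and ESS.

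**Working it through.** **1. Order of events.** Registration, T0, allocation (immediately after T0), allocation known to participants, W1. No diary week lies before allocation. For BDI-II, RIS and ESS the T0 value does lie before it. The baseline gap is therefore confirmed from the text and is limited to diary outcomes.

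**2. Counting e-mails and diaries.** Four diaries have 4 − 1 = 3 gaps. Four e-mails strictly between diaries need 5 diaries. With exactly four diaries and content in all four e-mails, two readings remain:
- (a) The first e-mail comes before or with W1 and the other three fill the gaps. W4 follows all content, but W1 is not treatment-free.
- (b) Each e-mail follows a completed diary, so the fourth follows W4. W1 precedes all content, but W4 precedes the last content, and so does T1 if it is taken at once. The Abstract, by contrast, places the post-assessment after completion of the program.

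A fifth diary would put W1 before all content and W5 after all of it. W1 would still follow open allocation.

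**3. What the W1 contrast estimates.** Let δ be the full effect on sleep efficiency, p1 and pL the shares of it present in W1 and in the last diary week, and b any between-arm difference in W1 that comes only from knowing the allocation. The between-arm difference in change is then

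(pL − p1)·δ − b.

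Under (a), p1 may exceed 0. Under (b), p1 = 0 but pL may be below 1. Both dilute the contrast. The term b can have either sign. None of p1, pL or b is given in the documents, so the net bias cannot be computed.

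**4. The plan's own sample size, reproduced.** Inputs from Methods: 3 groups, 2 measurements, r = .67, α = .05, power .80. The noncentrality is λ = f²·N·m/(1 − r), with df1 = (3 − 1)(2 − 1) = 2 and df2 = N − 3.
- f = 0.38, N = 15: λ = 0.1444 × 15 × 2/0.33 = 13.13, power 82.0%.
- f = 0.25, N = 30: λ = 0.0625 × 30 × 2/0.33 = 11.36, power 82.1%.
- Allocation target: 30/(1 − 0.5) = 60.

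All stated figures reproduce.

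**5. Illustration only.** Assume that the contrast loses a share of an effect of f = 0.25. A loss of 25% would correspond to one of four equally effective e-mails. The documents support neither that equality nor any particular share. At N = 30:
- 10% lost: f = 0.225, λ = 9.20, power 73%.
- 25% lost: f = 0.1875, λ = 6.39, power 56%.
- 40% lost: f = 0.15, λ = 4.09, power 38%.

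**The case against.** The strongest defence is that the timeline is not necessarily broken. Four diaries are a minimum, and an expected 6 to 12 weeks leaves room for a fifth. The first contact might be the message that opens the diary with instructions, leaving three content e-mails for three gaps. Fig. 1 and Table 2 are not shown and may fix the timing. A reader might infer that four e-mails cannot fit and that the effect must be misstated; the text does not support that. A fifth diary is not required, however, and sits uneasily with a T1 tied to the last of four, so the passages still need reconciling.

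Individual feedback presupposes diary data, so reading (b) is arguably the more natural. W1 would then precede all content, and its only weakness as a baseline would be that the arm is known. That is fair, although the references to a next e-mail and further content leave reading (a) open.

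The article labels no diary week as before or after, and the choice of weeks can be left to an analysis plan. This stands, but no analysis plan can supply a pre-allocation week that the sequence never collects.

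A reader might also infer that a seven-night average cannot be formed because breaks in the diary are permitted. This does not follow: breaks may fall between scored weeks, and an average can be taken over documented nights.

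Finally, the Abstract's list of primary outcomes names sleep quality rather than sleep efficiency, and the scales have a proper baseline. The baseline point therefore does not reach the whole trial.

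**Conclusion.** The absence of a pre-randomisation baseline for diary sleep efficiency in the online arms is certain from the text. An analysis of change from W1 would rest on a week recorded after open allocation and could be biased by an amount and in a direction that the documents do not allow to be computed.

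The e-mail timing is an unresolved inconsistency and does not prove that the effect is misstated. It does harm only if exactly four diaries are kept and all four contacts carry content. In that case either W1 is already treated, or W4 and T1 come before the last content can act.

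The power figures of 73%, 56% and 38% should not be read as a forecast. They rest on assumed shares, and the article does not say which outcome its feasibility effect size refers to. The sample size calculation itself stands as stated. The point deserves correction because a hypothesised outcome is affected and the remedy is cheap.

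**What to change.** **New participants.** Open the first diary week after T0 and allocate when that week is submitted, before any CBT-I content. Analyse the last diary week between arms with the pre-allocation week as covariate.

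**Participants already randomised.** Do not use W1 as baseline. Compare the last diary week between arms with T0 RIS as covariate; RIS was recorded before allocation. Analyse the two cohorts together with cohort as a factor or stratum.

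**Timeline.** Reconcile the Abstract with the Methods paragraphs on the course of the program and on the study design. State when each e-mail is sent relative to W1–W4 and T1 and which diary weeks enter the analysis. Place the final diary week and T1 after the last content, with matching assessment timing in the waiting list.

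**Cost.** An amendment, allocation about one week later, possibly one more diary week, and two cohorts with different baselines. Dropout during the first diary week would fall before randomisation in the new cohort and after it in the old one, so it must be reported by cohort. Recruitment began on 11/01/2019 and is planned to end on 05/31/2022, so the change helps only those still to be enrolled. A pre-allocation week also does not remove reporting differences in later weeks, because participants remain unblinded.

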**Table 2 Tab2:**
[figure not shown]
Schedule of enrolment, interventions, and assessments as recommended by the Standard Protocol Items: Recommendations for Interventional Trials (SPIRIT) statement [41]

*Optional CBT-I and T2 after waiting list not shown here in the interest of readability

The effect size for the CBT-I treatment in our feasibility study [29] (*n* = 22) was *d* = 0.76, corresponding to *f* = 0.38. The correlation among the repeated measures reached a value of *r* = .67. Setting the *α*-error probability at .05, *β*-error probability at .20, the number of groups at 3, and the number of measurements at 2, we calculated a required sample size of *N* = 15 using the ANOVA repeated measures, within-between interaction setting of the G*Power software [42]. If we adjust the effect size to a more conservative *f* = 0.25, the required sample size is *N* = 30. Consistent with this magnitude, Bortz and Schuster [43] recommend a sample size of at least *N* = 19 for large effect sizes, high power values, and low α-error probabilities. Expecting a maximum dropout rate of 50%, as observed in the feasibility study, we aim to allocate 60 participants and evaluate at least 30 participants (10 per group). We will make an effort to obtain assessments for participants who drop out of the study to facilitate carrying out intention-to-treat analyses.

Company physicians and social counseling services at collaborating companies will inform their workforce about the trial and screen those interested for eligibility. They will use flyers and posters to reach as many potential participants as possible, for example on company health days. They will also be the ones to obtain informed consent before granting access to our anonymous online platform. No personal information about potential or enrolled trial participants will be shared with the investigators. Vice versa, investigators will not share personal information with the company physicians and social counseling services. Exceptions to this rule are groups of at least ten participants, where sample characteristics, such as the average rate of improvement, may be communicated to the enrolling services in collaborating companies. No such data will be shared if inferences to individual cases are possible at any level or if any subsample of interest is smaller than ten.

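### The dropout contact recovers questionnaires but no diaries, so under the stated ANOVA sleep efficiency is compared only among participants with every diary week used

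*Protocol article*

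**What the plan says.** All references are to the Protocol article.

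- **Introduction, final paragraph.** The first of four hypothesised outcomes is "sleep efficiency as reported by the participants in sleep diaries". The other three are the BDI-II, RIS and ESS questionnaires.
- **Methods, outcomes paragraph.** "Outcome measures of the study will include data from at least four sleep diaries". Sleep efficiency is scored as "average sleep efficiency across seven consecutive nights", which is one diary week.
- **Methods, intervention paragraph.** An intervention counts as complete once the participant has "received all CBT-I contents and filled out at least 4 weeks of sleep diaries".
- **Methods, study design paragraph.** For the online arms, T1 is a psychometric assessment done "after filling out the last of four weekly sleep diaries (T1").
- **Methods, sample size (text after Table 2).** "Expecting a maximum dropout rate of 50%, as observed in the feasibility study", the plan allocates 60 to evaluate at least 30, 10 per group. It promises an effort to assess dropouts so that intention-to-treat analysis is possible.
- **Methods, data collection and analysis paragraphs.** That effort is specified as: "We will contact participants that dropped out or otherwise failed to transmit four sleep diaries for T1 measurements". Diaries are listed separately from the T0 and T1 data. Missing values are left unreplaced, dropouts get a separate analysis, and groups are compared by repeated measures ANOVA in SPSS.

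**The concern.** The contact is triggered partly by missing diaries, yet it collects something else. If every dropout answers, the three questionnaires are recovered and sleep efficiency is not. The intention-to-treat provision thus stops short of one of the four hypothesised outcomes.

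The stated analysis adds to this. Repeated measures ANOVA in its usual form drops anyone who lacks a value used in the test. Someone who sent weeks 1 to 3 but not week 4 leaves the comparison, and the three weeks sent are not used.

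Two things are at stake: precision in a small trial, and comparability of the arms. To send four diaries, an online participant must stay through sleep restriction, where the plan itself expects adverse events. A waiting-list participant only keeps a diary. Those left at week 4 may be selected differently in the two arms, and may differ from the population behind the questionnaire results.

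**Working it through.** **1. The plan's own figures.** Inputs from the sample size paragraph: α = 0.05, power 0.80, k = 3 groups, m = 2 measurements, ρ = 0.67. For the within-between interaction, λ = f²·N·m/(1 − ρ), df1 = (k − 1)(m − 1), df2 = (N − k)(m − 1).

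| f | N | power |
|---|---|---|
| 0.38 | 12 | 0.683 |
| 0.38 | 15 | 0.820 |
| 0.25 | 27 | 0.771 |
| 0.25 | 30 | 0.821 |

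Both stated sizes (15 and 30) reproduce, and 30/(1 − 0.50) = 60 reproduces the allocation target. The sample size is not in dispute.

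**2. How many could be affected.** At the maximum dropout, 60 × 0.50 = 30 could lack a full diary set. At assumed dropout of 10, 20, 30 and 40% the ceiling is 6, 12, 18 and 24 of 60. At f = 0.25 the three-group interaction has power 0.82 with 30 complete and 0.99 with all 60. These inputs are not specific to sleep efficiency, so the powers only show the scale of what incomplete data can cost.

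**3. What discarding transmitted weeks costs.** The article gives no dropout pattern for diaries, so this step rests on a simulation with assumed inputs:

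- 20 per arm (60/3), four weekly standardised values, and exchangeable correlation 0.67 (the plan's figure for its repeated measures, borrowed here for weeks).
- Monotone dropout after weeks 1, 2 and 3 with logit −1.35. The weekly probability is 1/(1 + e^1.35) = 0.206, and 0.794³ = 0.50 complete all four weeks.
- Comparison of four-week completers against maximum likelihood using every transmitted week.

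*Dropout unrelated to sleep efficiency.* With exactly 10 completers per arm, the week-4 standard error would be √(2/10) = 0.447 SD. Simulation, in which completer numbers vary, gave 0.465 for completers against 0.404 for all weeks: (0.465 − 0.404)/0.465 = 13%. A smaller run gave 0.425 against 0.381, or 10%. For W1-to-W4 change the reduction is about 5%.

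*Dropout dependent on the current week's sleep efficiency in the online arm only (log-odds 1 per SD).*

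| contrast | true value | completers | all weeks |
|---|---|---|---|
| Week-4 level | 0 | 0.34 to 0.35 | −0.02 to 0.00 |
| Week-4 level | 0.5 | 0.84 to 0.85 | 0.52 to 0.53 |
| W1-to-W4 change | 0 | −0.05 to −0.09 | −0.02 to 0.01 |

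The ranges are across runs. With the same dropout slope in both arms, the week-4 bias is about 0. In these scenarios dropout depends only on values already observed, which is the condition under which the likelihood model is valid. Its near-zero bias is therefore expected by construction.

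**The case against.** A reader might infer that sleep efficiency cannot be scored for half of those allocated. The text does not support that. Each seven-night diary gives a score, so anyone who sent one to three diaries has weekly values. The wording about at least four diaries describes the planned data and the completion rule, and nothing voids shorter sets. The 50% is a maximum and is not defined by diary count: a person with four diaries and no T1 could be a dropout with complete diary data.

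A reader might also infer a spurious online advantage of 0.35 SD. That holds only for a week-4 level contrast with outcome-related dropout in one arm, and no passage establishes that asymmetry. The article hypothesises greater improvement and sizes a two-measurement interaction, which points to change, with W1 as a natural baseline. There the bias is small and runs against the online arm: about 0.06 SD against a standard error of 0.38, roughly one-sixth of it.

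Finally, a condensed article may leave partial diary sets to a fuller document. That is fair as far as silence goes. It does not reach what the article does fix: the content of the dropout contact, no replacement, separate analysis of dropouts, and repeated measures ANOVA. Taken together, these set transmitted weeks aside.

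**Conclusion.** The point holds in limited form. The intention-to-treat effort does not extend to sleep efficiency, and the stated analysis reduces that outcome to participants with all the diary weeks used, while data already in hand are discarded. The ceiling is 30 of 60 allocated. The actual number is unknown and may be well below that.

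The firmest consequence is lost precision: a standard error about 10–13% smaller could be had for the week-4 contrast, and about 5% smaller for change. This assumes 20 per arm, correlation 0.67, half completing and unrelated dropout. Bias is conditional: about 0.35 SD in the week-4 level under one-sided informative dropout, near zero if dropout acts alike in both arms, and under 0.1 SD for change. The article does not say which diary contrast is tested, so which case applies cannot be settled from it. This is a worthwhile, inexpensive improvement; it does not show that the planned result would be wrong.

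**What to change.** - Define the outcome as weekly sleep efficiency at W1, W2, W3 and W4, and include every transmitted diary week from every randomised participant.
- Replace the complete-case repeated measures ANOVA for this outcome with a likelihood-based repeated-measures model containing arm, week and arm by week. Report the online versus waiting-list difference at W4 and in W1-to-W4 change.
- Keep four diaries only as a description of completion or adherence.
- Asking for a further diary week at the dropout contact is optional. If it is done, label that week as a later time point, not W4, because it follows a gap of unknown length. The model does not depend on it.

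The cost is mainly analysis wording. The model rests on a missing-at-random assumption: given the weeks already sent, stopping must not depend on the unseen later values. The optional diary week would add seven nights of recording for people who had already stopped. The change addresses the randomised comparison only; comparisons with the face-to-face group keep the confounding caveat that the article already gives.
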